## ****List of Abbreviations****

| **Abbreviation** | **Definition** |
| --- | --- |
| **ANSM** | National Agency for the Safety of Medicines and Health Products (Agence Nationale de Sécurité du Médicament) |
| **CA** | Competent Authority |
| **CRA** | Clinical Research Associate |
| **IB** | Investigator’s Brochure |
| **GMP** | Good Manufacturing Practices |
| **CHU** | University Hospital Center |
| **CNIL** | National Commission on Informatics and Liberty |
| **CPP** | Ethics Committee / Committee for the Protection of Persons |
| **CRF / eCRF** | Case Report Form / electronic Case Report Form |
| **INN** | International Nonproprietary Name |
| **AE** | Adverse Event |
| **SAE** | Serious Adverse Event |
| **PI** | Principal Investigator |
| **SmPC** | Summary of Product Characteristics |
| **VRB** | Volunteers for Biomedical Research |

**Full study synopsis**

| **SPONSOR** | University Hospital Center (CHU) of Lille |
| --- | --- |
| **LONG TITLE** | Sub-therapeutic GnRH-Antagonist Treatment to Rectify LH Pulsatility in Lean Women With PCOS |
| **SHORT TITLE** | GANIRELIX AND PCOS |
| **ACRONYM** | SOPKGANI |
| **STUDY CORDINATOR** | Prof. [name], MD, PhD, Department of Medical Gynecology, CHU de Lille |
| **MEDICAL CONDITION** | Polycystic Ovary Syndrome (PCOS) in women with AMH > 28 pmol/L, LH > 8 IU/mL, and serum testosterone > 0.39 ng/mL |
| **KEYWORDS** | PCOS; GnRH antagonist; LH; testosterone; androgens; FSH |
| **NUMBER OF CENTERS** | 1 (monocentric) |
| **SCIENTIFIC RATIONALE** | We will conduct a clinical study using low doses of a GnRH antagonist (Ganirelix) to reduce the abnormally high LH pulsatility in women with PCOS. By decreasing LH levels, we anticipate a reduction in androgen concentrations. The goal is to demonstrate that low-dose GnRH antagonists can reduce LH pulsatility by 20–30%, achieving values comparable to healthy women, and lower androgen levels by at least 20–30% without suppressing the hypothalamic-pituitary-gonadal axis or reproductive functions. |
| **PLAN EXPERIMENTAL** | **Pilot, phase 1, monocentric study with two parallel groups**, evaluating the efficacy of two doses of Ganirelix in reducing the frequency, mean and basal LH secretion in women with PCOS, in order to reach values comparable to those observed in healthy subjects (approximately 20–30% reduction).  The **European Medicines Agency (EMA)** medical report on Ganirelix safety data indicates no specific risk to humans based on conventional studies of safety pharmacology, repeated-dose toxicity, genotoxicity, carcinogenic potential, and reproductive toxicity. **Ganirelix is generally well tolerated**, even at higher concentrations (0.25 mg dose).  Participants included in the study will undergo **LH measurement every 10 minutes for 8 hours**, according to two phases:   - A **pre-treatment phase** of 4 hours; - A **post-treatment phase** of 4 hours, during which patients will receive one of the two Ganirelix doses.   **Androgens, FSH, AMH, and estradiol** will be measured at the start of the procedure (H0) and at the end (H8). |
| **STUDY ARMS AND TREATMENTS** | **Two experimental groups will be studied:**   - **Experimental Group 1:** Participants will be monitored for 4 hours without treatment, then will receive a dose of **0.0625 mg of Ganirelix**, followed by 4 additional hours of monitoring after injection. - **Experimental Group 2:** Participants will be monitored for 4 hours without treatment, then will receive a dose of **0.0250 mg of Ganirelix**, followed by 4 additional hours of monitoring after injection. |
| **STUDY PHASE** | Phase 1 |
| **OBJECTIVES AND EVALUATION CRITERIA** | ****Primary Objective**** To evaluate the effect of Ganirelix on the reduction of LH secretion frequency using two different doses. ****Primary Endpoint**** Aiming for a **20–30% reduction in LH pulse frequency** during the 4 hours following injection, to reach values comparable to those observed in healthy women. To be considered an LH pulse or peak, the value had to show an increase of more than 20% compared with one of the two preceding points, followed by a decrease of more than 10% in one of the two subsequent points. ****Secondary Objective No. 1**** To assess the variation in LH secretion (mean and basal secretion) before and after Ganirelix injection.  **Secondary Endpoint No. 1:** The variation in LH secretion before and after Ganirelix injection will be calculated as the mean LH (the average of all LH values over the study period) and basal LH, corresponding to the mean of the five lowest LH values over the study period. The total LH corresponds to the sum of all LH values at T0-T240 and T240-T480. ****Secondary Objective No. 2**** To evaluate the effect of two different doses of Ganirelix on androgen production.  **Secondary Endpoint No. 2:** Variation in androgen production 4 hours after injection, defined as the difference between total testosterone and androstenedione levels measured at H8 and H0 (4 hours before injection). ****Secondary Objective No. 3**** To evaluate the concentrations of FSH, estradiol, and AMH under low-dose Ganirelix at H0 and H8, before and after treatment.  **Secondary Endpoint No. 3:** Difference between the mean concentrations of FSH, estradiol, and AMH measured at H0 and H8. |
| **STUDY POPULATION** | ****Inclusion Criteria****  - Women aged **18 to 35 years** - Diagnosis of **PCOS** with **AMH > 28 pmol/L**, **LH > 8 IU/mL**, and **serum testosterone > 0.39 ng/mL** - **No hormonal treatment or contraception** for at least **2 months** prior to inclusion - **No treatment with Metformin** or any other medication affecting metabolism - **Affiliated with the French Social Security system** - **Body Mass Index (BMI)** below 30 **kg/m²**  ****Exclusion Criteria****  - **Pregnant women** - **Inability to understand the information leaflet** - **Known hypersensitivity** to Ganirelix, to any structural analog of gonadotropin-releasing hormone (GnRH), to exogenous peptide hormones, or to any of the excipients |
| **SAMPLE SIZE** | 20 women |
| **STATISTICAL ANALYSIS PLAN** | **General Principles** All statistical analyses will be performed independently by the Department of Biostatistics, University of Lille, under the supervision of [name]. Analyses will be conducted using 10.0.2 GraphPad Prism software (GraphPad; San Diego, CA, USA).  All analyses will be performed on the per-protocol population, unless otherwise specified. The level of statistical significance will be set at α = 0.05 (two-sided). No adjustment for multiple testing will be applied, and all secondary analyses will be considered exploratory. Results will be presented as effect size estimates with corresponding 95% confidence intervals (95% CI).  **Description of Data** Baseline demographic and clinical characteristics will be described by treatment group. Quantitative variables will be summarized as mean (standard deviation or standard error). The normality of data distributions will be evaluated using the Shapiro–Wilk test.  For normally-distributed data, data will be compared using unpaired two-sided Student’s *t*-test. For non-normally distributed values, Mann-Whitney U test will be used.  **Primary Endpoint Analysis** The primary endpoint is the reduction in LH pulse frequency during the 4-hour period following Ganirelix administration. Analysis will include: - Determination of LH pulse frequency using the method described above (1.1.2).  **Secondary Endpoint Analyses** - LH variation (mean, basal and total LH) before and after Ganirelix injection will be assessed. - Androgen production variation will be evaluated as the difference in total testosterone and androstenedione levels between H8 and H0 (4 hours post- vs. pre-injection). - FSH, estradiol, and AMH concentrations will be compared between H0 and H8 to assess hormonal changes after treatment.  **Handling of Missing Data** Given the short study duration and intensive monitoring, missing data are expected to be minimal. Any missing measurements will be described, and no imputation is planned. Analyses will be based on available data only.  **Statistical Software** All statistical analyses will be performed using: 10.0.2 GraphPad Prism software (GraphPad; San Diego, CA, USA)  **Justification for the Absence of a Power Calculation** As this is an **exploratory study** no formal sample size calculation or statistical power analysis has been performed. The main objective of this research is to generate preliminary physiological and pharmacodynamic data on the effect of low-dose Ganirelix on LH pulsatility in women with PCOS, rather than to formally test a hypothesis. Given the mechanistic and proof-of-concept nature of the study, the selected sample size of 20 participants is deemed appropriate to: - Evaluate feasibility and study logistics; - Provide initial estimates of variability in LH pulse frequency and amplitude under low-dose GnRH antagonist treatment; - Support the design of a future adequately powered confirmatory trial. This approach is consistent with international regulatory guidance for early-phase exploratory studies (ICH E9, EMA guidelines on exploratory trials), which emphasize estimation over formal hypothesis testing in pilot settings. |
| **STUDY TIMELINE** | Recruitment: 12 months Participant duration: 1 week Total study duration: 12 months + 1 week |
| **STUDY-SPECIFIC INVESTIGATION PROCEDURE AND DIFFERENCES COMPARED TO STANDARD CARE** | Standard treatment of endometriosis and stimulation protocols for IVF. Its use at a low dose is not common, nor is its use in women with PCOS (outside the context of endometriosis or an IVF protocol) |
| **ASSESSMENT OF THE BENEFITS AND RISKS RELATED TO THE RESEARCH** | **No individual benefit is guaranteed.**  **Risks related to the treatments:** A possible allergy to Ganirelix may occur, presenting as redness, warmth of the skin, itching, hives, nasal discharge, rapid or irregular pulse, swelling of the tongue and throat, sneezing, wheezing or significant breathing difficulties, or dizziness. Particular caution should be exercised in women showing signs or symptoms of an active allergic condition or with a known history of allergic predisposition. Treatment with Ganirelix is not recommended for women suffering from severe allergic conditions.  **Other risks described in the Summary of Product Characteristics (SmPC):**   - Skin irritation at the injection site: redness, itching, swelling; - Nausea; - Headaches.   **Risks related to blood sampling:** Blood collection may cause very slight discomfort, as samples are taken frequently, and minor bruising may appear at the site for a few days after the blood draw. |
| **SIMULTANEOUS PARTICIPATION IN ANOTHER STUDY** | **NO.** Participants enrolled in this study shall not, for the duration of the study, take part concurrently in any other interventional clinical trial involving investigational or marketed medicinal products. |
| **EXCLUSION PERIOD FOLLOWING THE STUDY** | **NO.** |
| **JUSTIFICATION FOR WHETHER OR NOT A MONITORING COMMITTEE IS ESTABLISHED** | In view of the existing data on Ganirelix and the low doses administered to patients enrolled in this study, the establishment of a Safety Monitoring Committee is deemed unnecessary. |
| **FUNDINGS SOURCES** | Horizon-ERC-POC grant (ERC-2022-POC2 to [name], grant agreement n° 101111874/GRASP) |
| **HEALTH TECHNOLOGY MATURITY LEVEL (TRL)** | TRL 6c |

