# EVALUATION CRITERIA

### ****4.1 Endpoint for the Primary Objective****

The expected decrease in LH pulse frequency before and after Ganirelix* administration is estimated to be between 20% and 30%.
To be considered an LH pulse or peak, the value had to show an increase of more than 20% compared with one of the two preceding points, followed by a decrease of more than 10% in one of the two subsequent points.

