# METHODOLOGY

### ****5.1 Study Design****

This is a **single-center, phase I pilot study** with **two parallel groups**.

The study will be proposed during endocrinological gynecology consultations to all patients meeting the inclusion criteria. After obtaining written informed consent, participants will be assigned to one of the two dose groups.

During the 4 hours preceding Ganirelix injection*, baseline LH secretion and pulsatility, as well as baseline levels of androgens, FSH, estradiol, and AMH, will be measured.

Subsequently, patients will receive a **low-dose injection of Ganirelix***. LH secretion and pulsatility will be monitored for **4 hours following the injection**, along with measurements of androgens, FSH, estradiol, and AMH at **H8**.

The expected outcome is to identify the Ganirelix* dose that reduces the abnormal frequency of LH pulses in women with PCOS to values comparable to normal conditions (approximately a 30% reduction).

As **secondary outcomes**, reproductive markers (serum levels of testosterone, androstenedione, LH, FSH, estradiol, and AMH) as well as glucose, insulin, and liver function parameters will be assessed before and after the 4-hour GnRH antagonist treatment period.

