### ****5.2 Measures Taken to Minimize Bias****

Each participant will serve as her own control in this study, thereby minimizing potential bias.

The phenotypic diversity among women with PCOS — particularly regarding lean versus obese status — has a significant impact on mean plasma LH levels. To reduce variability, this pilot study will focus exclusively on **lean women with a highly uniform PCOS phenotype**, defined as follows:

- Age between **18 and 35 years**,
- **BMI below 30 kg/m²**,
- **Hyperandrogenism** (total testosterone > 0.39 ng/mL),
- **Elevated plasma LH** (> 8 IU/mL),
- **Elevated plasma AMH** (> 28 pmol/L).

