### ****7.2 Study Procedures****

This is a **phase 1 pilot study** with **two parallel groups**, evaluating the efficacy of two different doses of Ganirelix in **20 women with PCOS**, defined by **oligo-/anovulation**, **hyperandrogenism**, and **elevated circulating LH levels**.

An **intravenous cannula** will be inserted, and **blood samples will be collected every 10 minutes** for a **4-hour baseline period** starting at 8:00 a.m.
Subsequently, Ganirelix will be administered as a **single subcutaneous injection** at one of two doses:

- **0.025 mg** (n = 10 PCOS patients)
- **0.0625 mg** (n = 10 PCOS patients)

These doses correspond to approximately **one-tenth and one-quarter** of the standard clinical dose used in **IVF protocols** to achieve full LH suppression.

Following Ganirelix administration, blood sampling will continue every 10 minutes for an additional **4-hour period**.

The **primary endpoints** include mean LH levels, as well as LH pulse **frequency and amplitude**, evaluated before and during treatment with Ganirelix.
In healthy women, LH surges occur approximately every 90 minutes during the early follicular phase, whereas **lean women with PCOS** may exhibit **one or more LH pulses per hour**.

The expected outcome is to determine the Ganirelix dose that reduces the **abnormally elevated frequency** of LH pulses by approximately **20–30%**, bringing them closer to normal physiological values.

**Secondary outcomes** include reproductive hormone markers — **serum testosterone, androstenedione, LH, FSH, estradiol, and AMH levels** — measured before treatment and **4 hours post-injection**.

The **pretreatment period** (baseline LH secretion and pulsatility) will be compared to the **4-hour post-antagonist period.**An **LH pulse** will be defined as a **≥20% incremental change** in LH concentration between the nadir and the subsequent peak, as previously described in similar clinical studies (Ref. 25).

The degree of gonadotropin suppression will be calculated as a **percentage of inhibition** relative to the pre-antagonist period:

$$\text{Inhibition (\%)}=\frac{(\text{PRE mean}-\text{nadir})}{\text{PRE mean}}\times100$$

as described previously (Ref. 26).
Hormone nadir levels will be computed using a **moving average**.
For LH, a **6-point moving average** (equivalent to 1 hour of sampling) will be used, as the nadir is expected to occur within the 10-minute sampling intervals.

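### The primary endpoint and the dose-identification outcome aim at healthy or normal LH pulse values, but the trial has no healthy reference able to support that conclusion, and a 20–30% fall does not stand in for one

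*Protocol*

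**What the plan says.** The healthy benchmark appears at three levels of the protocol.

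- **Goal.** In the synopsis, the Scientific Rationale and Plan Experimental rows equate a reduction of about 20–30% with reaching the values of healthy women.
- **Primary endpoint.** The synopsis describes a 20–30% reduction in pulse frequency "during the 4 hours following injection, to reach values comparable to those observed in healthy women".
- **Dose identification.** Section 5.1 expects to find the dose that "reduces the abnormal frequency of LH pulses in women with PCOS to values comparable to normal conditions", which it puts at roughly a 30% reduction.

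The comparator is described in section 5.2: "Each participant will serve as her own control in this study". All 20 participants have PCOS (sections 5.3 and 7.2), and no healthy woman is sampled.

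The only healthy pulse rate is in section 7.2: "In healthy women, LH surges occur approximately every 90 minutes during the early follicular phase". The same sentence says that lean women with PCOS may show "one or more LH pulses per hour". It carries no citation, spread, sampling interval or detection method.

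The trial's own counts come from a specific rule. Under section 4.1, "the value had to show an increase of more than 20% compared with one of the two preceding points", and a fall of more than 10% must follow within two points. Section 7.2 gives a different rule, a "≥20% incremental change" from nadir to peak, with no requirement for a subsequent fall.

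Section 4.1 and the Statistical Analyses section describe the primary endpoint as the reduction alone. No section says what range of values would count as comparable.

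**The concern.** A within-woman percentage change needs no outside reference, because the same rule is applied before and after injection. A statement that women have reached healthy values does need one. It requires a healthy rate obtained in a way that can be set beside the trial's counts, and a range within which two rates are called comparable. The protocol supplies neither.

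At stake is what the trial may conclude. Read as written, an observed fall of 20–30% would be reported as normalisation, and a dose would be identified on that basis and carried into the later confirmatory trial that the pilot is meant to support. A statistical analysis plan could define a range for comparable. It could not supply healthy series that the design neither collects nor cites.

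**Working it through.** **Step 1. Is the percentage target the same as the healthy value?**

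Inputs: healthy interval about 90 minutes; PCOS rate at least 1 per hour (both section 7.2); observation window 240 minutes; target reduction 20–30% (synopsis), about 30% (section 5.1).

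Healthy rate per 4 hours = 240/90 = 2.67.

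Reduction needed = 1 − 2.67/(4 × PCOS pulses per hour).

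| PCOS rate before injection | Per 4 h | After 20% fall | After 30% fall | Fall needed to reach 2.67 |
|---|---|---|---|---|
| 1.0 per hour | 4.0 | 3.2 | 2.8 | 33.3% |
| 1.25 per hour | 5.0 | 4.0 | 3.5 | 46.7% |
| 1.5 per hour | 6.0 | 4.8 | 4.2 | 55.6% |

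The first row follows directly from the protocol's rates. The other two illustrate its wording that the rate may exceed one per hour. In the first row the resulting intervals are 240/3.2 = 75 minutes and 240/2.8 = 86 minutes.

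Working backwards, a 20% fall reaches one pulse per 90 minutes only from (60/90)/0.8 = 0.83 per hour, and a 30% fall only from (60/90)/0.7 = 0.95 per hour. Both starting rates are below the one per hour that section 7.2 gives for PCOS.

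So the protocol's equation of 20–30% with healthy values is not reproduced from its own figures. At exactly one pulse per hour the 30% end misses by only 2.8 − 2.67 = 0.13 pulses per 4 hours, which the word approximately could cover. The 20% end misses by 0.53, and the gap widens at higher starting rates.

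**Step 2. Can 2.67 be set beside counts from the section 4.1 rule?**

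The documents do not say how the 90-minute figure was obtained, so this cannot be answered from them. Simulation can only show whether the counting method could matter. None of the simulation inputs below is in the protocol. A point was flagged if it exceeded one of the two preceding points by more than 20% and one of the two following points was more than 10% lower.

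- *First set:* 18 combinations of pulse height 30–100% of baseline, decay half-life 60–80 minutes and assay CV 3–8%, with 20% variation in interval; 8-hour series, counts averaged per 4 hours. With adjacent flags merged into one pulse, a true 90-minute rhythm (2.67) scored 0.51–2.55 and a true 60-minute rhythm (4.0) scored 0.65–3.57. Without merging, the ranges were 0.55–3.62 and 0.71–5.68.
- *Second set:* a single 4-hour window of 25 samples, half-life 60 minutes, 25% variation in interval, adjacent flags merged. With pulse height 1.0–1.5 times baseline and CV 3–8%, the 60-minute rhythm scored 2.4–3.0 and the 90-minute rhythm 1.6–2.2. Flat LH with no pulses scored 0.0 at CV 3%, 0.1 at 5%, 0.8 at 7%, 1.3 at 8% and 2.3 at 10%.

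Scored counts can therefore lie well below or above the true frequency. The direction depends on pulse height, assay noise and whether adjacent flags are merged, which section 4.1 does not state. These results illustrate that the rule matters. They do not estimate the error in this trial.

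**The case against.** The strongest reply is that no planned analysis uses 2.67. Section 4.1 and the Statistical Analyses section speak only of the reduction, section 7.2 compares the periods before and after injection and speaks of moving closer to normal, and the synopsis words the healthy value as an aim. This stands. A reader might infer that the endpoint will be tested against one pulse per 90 minutes and that normalisation will be declared by that test. The documents contain no such test.

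A reader might also infer that the 90-minute figure and the trial's counts are on different scales. That is not shown either. The figure's scoring is unstated, it may itself come from a threshold rule, and it stands in the same sentence as the PCOS rate. What is supported is that comparability is unknown.

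The simulated sizes depend on chosen inputs. In 8 of the 18 combinations in the first set, with flags merged, an untreated hourly rhythm already scored at or below 2.67. That is a tally of chosen settings, not a probability, and it fixes neither the size nor the direction of an error.

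A further defence is that the percentage is the working definition of healthy, as where section 5.1 writes "to values comparable to normal conditions (approximately a 30% reduction". Step 1 answers this: on section 7.2's own rates, 20–30% stops short.

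Finally, this is an exploratory pilot that promises effect estimates with 95% confidence intervals. That limits the damage, but it also favours removing a claim that estimation in these 20 women cannot support.

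**Conclusion.** The concern holds for the claim of reaching healthy or normal values, in the goal, the primary endpoint and the dose-identification outcome. It does not extend to the whole endpoint: the within-woman change needs no healthy control.

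The firm part rests on the documents alone. There is no healthy sample and no range for comparable. The single healthy rate has no stated source or method. On the protocol's own rates, the 20–30% target leaves at least 3.2 to 2.8 pulses per 4 hours against 2.67, so at least a 33% fall is needed. That arithmetic takes the 90-minute and one-per-hour figures at face value, although section 7.2 gives the first as approximate and the second as what may occur.

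How far counts under the trial's rule depart from the healthy reference cannot be determined from the documents.

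**What to change.** In the synopsis (Scientific Rationale, Plan Experimental and Primary Endpoint) and in sections 5.1 and 7.2, remove reaching or approaching healthy or normal values from the endpoint and from what the trial will conclude, including the basis on which a dose is identified.

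State the primary result as the within-woman change in LH pulse frequency from the 4 hours before to the 4 hours after injection, by dose, with its 95% confidence interval.

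If a healthy reference is kept, make it descriptive, and state its source, sampling interval and pulse rule. Preferably use existing healthy series re-scored with the trial's rule. The rules in sections 4.1 and 7.2 must first be reconciled into one.

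The change is to wording, with no extra patients or samples. The cost is that the trial gives up the normalisation claim; re-scoring healthy series would depend on obtaining them. The fix does not address whether the scored count itself falls when pulse amplitude falls, which is a separate issue.
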